### Elimination Criteria

(1) Subjects don't meet the inclusion criteria but they are included in the trial by mistake;(2) Subjects don't follow the prescribed treatment or have incomplete data that affects the efficacy evaluation and safety evaluation;(3) Subjects with poor compliance and withdraw from the study by themselves;(4) Subjects received adjunctive treatments other than the intervention of this trial.

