### Discontinuation Criteria

(1) Subjects have serious adverse reactions during the study and it is not appropriate to continue participating in the trial;(2) Subjects have serious complications or deteriorating conditions during the study and emergency measures are urgently needed;(3) Subjects ask to quit the trial halfway;(4) Subjects have poor compliance and cannot comply with the study protocol.

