##### (2) Operation

Patients are asked to select the appropriate body position in terms of HZ sites, such as lateral, supine and prone positions, etc. The skin around the selected acupoint is routinely disinfected. Patients are then given acupuncture and deqi sensation is achieved in all acupoints. Two paired of acupoints (i.e., two Jiaji acupoints and two Ashi points, respectively) are connected to the EA apparatus. EA parameter is selected as dilatational wave and frequency is 2/100 Hz. EA intensity is determined according to patients' endurance.

Needles will be retained and EA will last for 30 min for each session. Patients will receive a total number of 30 EA sessions, with the frequency of 5 sessions per week for 6 weeks.

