#### Secondary Outcome Measures

(1) Change in dosage of prescription analgetic;(2) Change in quality of life measure by 36-item short form health survey (SF-36);(3) Change in anxiety and depression severity measure by hospital anxiety and depression scale (HADS);(4) Change in sleep quality measured by Pittsburgh sleep quality index (PSQI)

Secondary outcomes will be assessed before intervention, at 2, 4, 6 weeks after intervention and at the end of 8-week follow-up.

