### Limitations

First, given to the characteristic of acupuncture procedure as well as the complete difference between the two therapies in two groups (i.e., pharmacotherapy vs. non-pharmaceutical therapy involving complex procedures), it is difficult to blind acupuncture operator and patients in our study. Nevertheless, the purpose of blinding aims to avoid the effect of subjective factors from the researchers and participants on the study results. With the attempt to minimize the subjective influence, in our study outcome assessment and statistical analysis will be implemented by a third party who is blinded to the grouping.

Second, sham acupuncture is not selected as a control in our study due to two major considerations: (1) owing that acupuncture is well-accepted and widely used in 3 sub-centers that enroll participants, the vast majority of participants have rich experience of acupuncture, even if a sham acupuncture group is designed, complete blinding of participant remains difficult to achieve in our study. (2) Previous studies reveal that all types of sham acupuncture currently available are not completely inert, regarding of penetrating or non-penetrating, thereby all current modalities of sham acupuncture have positive treatment effects (40–42). In this scenario, the treatment effect of verum acupuncture is likely to be underrated when compared with sham acupuncture (43). Therefore, sham acupuncture is not selected the control in our study. Nevertheless, when interpreting study results in the future, extra considerations should be given to the psychological (non-specific) effects of acupuncture that may influence the treatment effect, such as participants' expectations and the doctor–patient interaction in acupuncture procedures.

Third, due to the funding of this study, the follow-up period only covers 8 weeks. The longer-term therapeutic effect of EA on PHN needs further investigation. And only 3 centers involve patient enrollment.

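### The elimination criteria remove randomised patients for events after randomisation, and nothing confines this to a secondary analysis

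*Protocol article*

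**What the plan says.** The protocol article has two separate lists. Discontinuation Criteria says when a subject stops taking part, and already covers quitting and non-compliance ("Subjects have poor compliance and cannot comply with the study protocol"). Elimination Criteria follows with four grounds:

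- Criterion 1: subjects who do not "meet the inclusion criteria but they are included in the trial by mistake".
- Criterion 2: subjects who do not "follow the prescribed treatment or have incomplete data that affects the efficacy evaluation and safety evaluation".
- Criterion 3: "Subjects with poor compliance and withdraw from the study by themselves".
- Criterion 4: "Subjects received adjunctive treatments other than the intervention of this trial".

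Statistical Analysis names the tests but no analysis population. Quality Control says only that dropouts and withdrawals are recorded. Sample Size Estimation requires 57 per group and enrols 66 per group to allow for 15% dropout.

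**The concern.** Criterion 1 rests on a fact fixed before randomisation and is not at issue. Criteria 2 to 4 rest on what patients do afterwards, and what they do can depend on the arm and on how well they are doing.

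Only the EA arm has a visit schedule to fail: "Patients will receive a total number of 30 EA sessions, with the frequency of 5 sessions per week for 6 weeks". Patients know their arm, since the Limitations section concedes that "it is difficult to blind acupuncture operator and patients in our study". A patient whose pain persists may stop attending, withdraw, or look for other treatment, and the rates may differ between arms.

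If such patients are removed, the groups compared are no longer the groups randomised. Blinded assessors and statisticians do not prevent this, because the selection happens before the comparison is made. Criterion 2 also names the safety evaluation. As worded, it could take out patients whose data are incomplete, and some of them may have stopped because of an adverse event.

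**Working it through.** **Reading the text**

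1. Stopping is dealt with under Discontinuation Criteria, so a second list must do something else.
2. Criterion 2 is tied to the efficacy and safety evaluations. The natural reading of elimination is therefore removal from the evaluated data, although the article never says what subjects are eliminated from.
3. No section mentions intention-to-treat, analysis as randomised, or a per-protocol set to which the list would apply.

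**The plan's own figure**

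Inputs from Sample Size Estimation: 57 per group, 15% dropout, α = 0.05, β = 0.2 (two-sided testing assumed).

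- 57 × 1.15 = 65.55, rounded up to 66 per group and 132 in total. The stated size reproduces.
- 66 × 0.85 = 56.1 per group remain. The plan thus counts on about 57 evaluable patients per group, which is consistent with analysing those who are left.
- The pilot difference and SD are not printed. The implied standardised difference is (1.960 + 0.842) × √(2/57) = 0.525 by the normal formula and 0.529 by the t distribution, so about 0.53 SD.

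**Illustration of the possible bias**

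Assumptions, none of them from the documents: a normal outcome with SD 1, no true effect, 66 per arm, and elimination of the lowest fraction p of a score that correlates ρ = 0.5 with the outcome.

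The mean of the patients who remain in an arm rises by

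ρ × φ(z_p) / (1 − p),

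where z_p is the p-quantile of the standard normal and φ its density. With ρ = 0.5 the shift is 0.054 SD at p = 5%, 0.097 at 10%, 0.137 at 15%, 0.175 at 20% and 0.212 at 25%. The bias is the difference between the arms' shifts. Type I error comes from simulating a two-sided 5% two-sample test.

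| Eliminated (one arm / other arm) | Bias, formula (SD) | Type I error, simulated |
|---|---|---|
| None | 0 | about 5% |
| 15% / 15%, unrelated to outcome | 0 | about 5% |
| 15% / 15%, same outcome-related process | 0.137 − 0.137 = 0 | about 6% |
| 20% / 10% | 0.175 − 0.097 = 0.08 | about 8% |
| 15% / 15%, outcome-related in one arm only | 0.137 − 0 = 0.14 | about 12% |
| 25% / 5% | 0.212 − 0.054 = 0.16 | about 14% |

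In the 20% / 10% row the simulated bias is 0.07, because whole patients are removed (13 and 7 of 66). The largest bias is 0.16 / 0.53 = 30% of the implied design difference. Swapping the arms reverses its sign.

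**The case against.** **The analysis population belongs in the statistical analysis plan (SAP), and such a list may be meant for a per-protocol set.** A missing definition alone would be no finding. Here, however, the protocol states a removal rule and nothing limits it. A SAP that follows the rule inherits the problem, and a SAP that analyses everyone as randomised contradicts the rule. The objection lowers certainty about intent but does not remove the need to change the text.

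**The direction is unknown.** This stands. Visit burden could raise non-adherence in the EA arm. Equally, patients on medication alone may be disappointed and withdraw or seek other treatment, and the article says acupuncture is well accepted at these centres. Removing poor responders flatters whichever arm loses more of them, so a reader should not infer that the rule favours EA.

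**A larger bias could be inferred.** If 15% were lost from one arm only, and these were exactly its worst responders, that arm's mean would shift by 0.27 SD and the simulated type I error would be about 38%. The documents do not support this as a headline. The 15% in Sample Size Estimation applies to both groups, and perfect selection on outcome in one arm alone is a corner case.

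**A conflict between criterion 4 and a secondary outcome could be inferred.** The outcome is "Change in dosage of prescription analgetic". It can be read as the titrated gabapentin dose, which is part of the trial intervention in both arms and so outside criterion 4. No contradiction is shown.

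**The safety effect is inference.** This stands in part. Serious adverse reactions come under the discontinuation list, and Safety Evaluation says events throughout the study are recorded. Nothing says that a patient who stops for an adverse event is eliminated. What remains is that criterion 2 names the safety evaluation and does not exclude that reading.

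**Conclusion.** The concern holds. Followed as written, criteria 2 to 4 give a comparison of selected patients in an open-label trial whose two primary outcomes rest on patients' own reports and perceptions. That is a rule the protocol states, and the protection of randomisation is lost under it whether or not bias then follows.

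The size cannot be known in advance. Bias arises only if elimination is related to outcome and differs between arms. Under the assumptions shown, it runs from about 0 to about 0.16 SD in either direction, with a type I error of about 6% to 14%, against an implied design difference of about 0.53 SD. The elimination rates and the 0.5 correlation are assumed. For safety, the conclusion is only that the wording permits removal of patients with incomplete data.

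**What to change.** In the protocol, and in the SAP to match, state that:

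1. The primary efficacy analysis includes all randomised patients in their assigned arm, whatever their adherence, adjunctive treatment or early stopping.
2. The safety analysis includes everyone who received any study treatment.
3. The Elimination Criteria define only a secondary per-protocol set.
4. The scheduled assessments at weeks 2, 4, 6 and 14 continue after study treatment stops, unless the patient withdraws consent for data.

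The fourth item needs to be in place during the trial, because outcomes not collected cannot be recovered later. Handling of values that are still missing can be left to the SAP.

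The cost is wording, a few more assessments, and possibly a smaller estimated effect. No more patients are needed. At the implied difference of 0.525 SD, power is 79.3% with 56 per group and 85.4% if all 66 per group are observed. The latter is an upper bound, since including non-adherent patients may dilute the effect.

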### Randomization and Allocation Concealment

All patients will be randomly assigned to either the EA combined with medication group or medication group via a computerized central randomization system. If a participant is enrolled, an independent researcher in each center, who has no contact with participants, acupuncturists and outcome assessors, will log into the computerized central randomization system to generate random sequence, dividing eligible participants into two groups in a ratio of 1:1. The researcher will make random allocation cards, each with its group allocation information and sealed into an opaque envelope, which will not be open until the first treatment.

### Blinding

Given to the characteristics of acupuncture, acupuncture manipulators will not be blinded. Nevertheless, the treatment, outcome assessment, and statistical analysis will be performed by different researchers independently. Outcome assessment will be performed by assessors blinded to the allocation information. Statistical analyses will be performed by statisticians blinded to the allocation information.

### Intervention

Participants will receive either EA combined with medication or medication alone.

The treatment course of both groups is up to 6 weeks and the follow-up period is 8 weeks.

#### EA Combined With Medication Group

Patients in this group received EA combined with gabapentin. Gabapentin is administrated as described in 2.8.2. Acupuncture will be performed with needles in the specification of 0.30 × 40 mm (Suzhou Medical Products Factory Co., Ltd, China). EA procedures will be performed with electronic needle instruments (Hans-100A, Nanjing Jisheng Medical Technology Co., Ltd, China).

##### (1) Acupoint Selection

The location standard of acupoints is based on the National Standard Nomenclature and Location of Acupuncture Points 2006 (GB/T12346-2006). Locations of acupoints applied in this trial are summarized in Table 3.

**Table 3 T3:** Location and indication of acupoints for treating PHN.

**Acupoints**	**Location**	**Indication**
**Primary acupoints**		
(1) Ashi acupoints	Ashi points are defined as the most painful points in the herpes zoster lesion are.	**–**
(2) Jiaji acupints (EX-B2)	Jiaji acupoints on the ipsilateral side will be selected according to the corresponding ganglia involved by herpes zoster. Jiaji acupoints (EX-B2) are located 0.5 cun bilateral to the posterior midline in the dorsal thoracic and lumbar region, ranging from the first thoracic vertebra to the fifth lumbar vertebra.	–
(3) Xi-cleft points		
Waiqiu (GB36)	On the lateral aspect of the lower leg, 7 cun above the tip of the external malleolus, on the anterior border of the fibula, at the level of GB 35.	For pain sites that mainly distributed in the gallbladder meridian
Liangqiu (ST34)	When the knee is flexed, on the anterior aspect of the thigh, on the line connecting the anterior superior iliac spine and the lower lateral border of the patella, 2 cun above the patella.	For pain sites that mainly distributed in the stomach meridian
Jinmen (BL63)	On the lateral aspect of the foot, directly below the anterior border of the external malleolus, lateral to the lower border of the cuboid bone.	For pain sites that mainly distributed in the bladder meridian
Wenliu (LI7)	With the elbow flexed, the point is on the dorsal radial side of the forearm, 5 cun above the wrist crease	For pain sites that mainly distributed in the large intestine meridian
**Supplementary acupoints**		
Xingjian (LR2)	On the dorsum of the foot, proximal to the margin of the web between the 1st and 2nd toes, at the junction of the red and white skin.	For stagnated heat of the liver meridian
Yinlingquan (SP9)	On the medial aspect of the lower leg, in the depression of the lower border of the medial condyle of the tibia.	For damp heat of the spleen meridian
Geshu (BL17)	On the back, 1.5 cun lateral to the lower border of the spinous process of the 7th thoracic vertebra.	For blood stasis obstruction in vessels
Sanyinjiao (SP6)	On the medial aspect of the lower leg, 3 cun above the medial malleolus, on the posterior border of the medial aspect of the tibia.	For Yin deficiency of liver and kidney

Primary acupoints include Ashi points, Jiaji acupoints (EX-B2) and Xi-cleft acupoints. Ashi points are defined as the most painful points in the HZ lesion area and the selection number of Ashi points will be controlled within 3 for each treatment session. Jiaji acupoints (EX-B2) on the ipsilateral side will be selected according to the corresponding ganglia involved by HZ. Xi-cleft acupoints will be selected based on the distribution regions of PHN. For pain sites that mainly distributed in the gallbladder meridian, Waiqiu (GB36) will be selected. For pain sites that mainly distributed in the stomach meridian, Liangqiu (ST34) will be selected. For pain sites that mainly distributed in the bladder meridian, Jinmen (BL63) will be selected. For pain sites that mainly distributed in the large intestine meridian, Wenliu (LI7) will be selected.

Supplementary acupoints will be chosen based on TCM syndrome differentiation. For stagnated heat of the liver meridian, Xingjian (LR2) will be selected. For damp heat of the spleen meridian, Yinlingquan (SP9) will be selected. For blood stasis obstruction in vessels, Geshu (BL17) will be selected. For Yin deficiency of liver and kidney, Sanyinjiao (SP6) will be selected.

##### (2) Operation

Patients are asked to select the appropriate body position in terms of HZ sites, such as lateral, supine and prone positions, etc. The skin around the selected acupoint is routinely disinfected. Patients are then given acupuncture and deqi sensation is achieved in all acupoints. Two paired of acupoints (i.e., two Jiaji acupoints and two Ashi points, respectively) are connected to the EA apparatus. EA parameter is selected as dilatational wave and frequency is 2/100 Hz. EA intensity is determined according to patients' endurance.

Needles will be retained and EA will last for 30 min for each session. Patients will receive a total number of 30 EA sessions, with the frequency of 5 sessions per week for 6 weeks.

#### Medication Group

Participants in the medication group will only receive oral administration of gabapentin capsule. The dosage of gabapentin starts from 100 mg Tid. 100–300 mg can be increased every 3–7 days and taken in three doses, but the total amount is not more than 1,800 mg/day. The dosage of gabapentin will be adjusted according to the patient's condition until his pain is effectively controlled.

After maintaining the medication for 2 weeks, the dosage can be gradually reduced and 100 mg can be reduced every 3–7 days.

### Outcome Measures

#### Primary Outcome Measures

(1) Change in sensory perception measured by quantitative sensory testing (QST);QST is a psychophysical test method that investigates the functional state of the somatosensory system by means of calibrated stimuli and subjective perception thresholds (13). It is a valid and reliable test method that is often adopted in trials involving HZ or PHN (14, 15). QST will be performed in accordance with the protocol developed by the German ResearchNetwork on Neuropathic Pain (DFNS) that was described in details elsewhere (16) and in brief, multiple tests will be performed as supplied in Appendix 1.(2) Change in pain intensity measured by Zoster Brief Pain Inventory (ZBPI) instrumentZBPI is a herpes zoster specific questionnaire to quantify pain and discomfort in HZ and PHN patients. The validity and reliability of the ZBPI as an outcome measure for HZ or PHN has been proved (17), so it is frequently used in trials involving PHN patients (18, 19). The detailed questionnaire of ZBPI is supplied in Appendix 2.

Primary outcomes will be assessed before intervention, at 2, 4, 6 weeks after intervention and at the end of 8-week follow-up.

#### Secondary Outcome Measures

(1) Change in dosage of prescription analgetic;(2) Change in quality of life measure by 36-item short form health survey (SF-36);(3) Change in anxiety and depression severity measure by hospital anxiety and depression scale (HADS);(4) Change in sleep quality measured by Pittsburgh sleep quality index (PSQI)

Secondary outcomes will be assessed before intervention, at 2, 4, 6 weeks after intervention and at the end of 8-week follow-up.

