## Abstract

**Introduction:** The efficacy of conventional treatments for treating postherpetic neuralgia (PHN) remains unsatisfactory. Thus, this multicentre, randomized controlled, assessor-blinded trial aims to investigate the efficacy and safety of electroacupuncture (EA) therapy in patients with PHN.

**Methods and Analysis:** This multicentre randomized controlled trial will enroll 132 patients with PHN from 3 hospitals. All patients will be randomly assigned to either the EA combined with medication group or medication group through a computerized central randomization system in a 1:1 ratio. Outcome measures will be assessed before intervention, at 2, 4, 6 weeks after intervention and at the end of 8-week follow-up. Primary outcomes will be sensory thresholds and pain intensity. Secondary outcomes will include dosage of analgetic, quality of life, anxiety, and depression severity and sleep quality. All adverse effects will be assessed during the trial.

**Conclusions:** This study will provide evidence to ascertain whether EA is effective and safe for treating PHN.

**Ethics and Dissemination:** Ethics approval (No.ZSLL-KY-2017-025) has been obtained from the Ethics Committee of The Third Affiliated Hospital of Zhejiang Chinese Medical University. Informed consent will be signed prior to subject enrolment. The results will be submitted to international peer-reviewed journals and presented at international conferences.

**Trial Registration Number:** The study protocol has been registered in the clinicaltrials registry with the identification code NCT04594226.

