**Outcome assessment**						
(1) QST		○	○	○	○	○
(2) ZBPI		○	○	○	○	○
(3) Dosage of analgetic		○	○	○	○	○
(4) SF-36		○	○	○	○	○
(5) HADS		○	○	○	○	○
(6) PSQI		○	○	○	○	○
Safety assessment			○	○	○	○
Recurrence of PHN						○

*○, required; HADS, Hospital Anxiety and Depression Scale; PHN, postherpetic neuralgia; PSQI, Pittsburgh Sleep Quality Index; QST, Quantitative Sensory Testing; SF-36, Short Form 36 Health Survey; ZBPI, Zoster Brief Pain Inventory*.

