### Sample Size Estimation

The participants will be assigned to 2 groups in a ratio of 1:1. The sample size is calculated based on the change of ZBPI from baseline to 6 weeks after intervention, the results of which are acquired from our pilot study. It is assumed that n_1_ = n_2_, α = 0.05, and β = 0.2. Thus, each group approximately requires 57 participants. With an estimated dropout rate of 15%, a total of 132 subjects are needed, with 66 participants in each group.

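### The analgesic outcome counts only prescription drugs in its definition but not in the abstract or Table 1, and other pain relief leads to elimination, so the dose recorded cannot stand for total analgesic need

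*Protocol article*

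**What the plan says.** All references are to the protocol article.

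- **Secondary Outcome Measures** lists "Change in dosage of prescription analgetic" as the first secondary outcome, measured before the intervention, at weeks 2, 4 and 6, and at the end of the 8-week follow-up.
- **Abstract:** "Secondary outcomes will include dosage of analgetic", with no mention of prescription.
- **Table 1** has the row "3) Dosage of analgetic", again unqualified, marked at weeks 0, 2, 4, 6 and 14.
- **Elimination Criteria**, fourth item: "Subjects received adjunctive treatments other than the intervention of this trial".
- **Medication Group:** "Participants in the medication group will only receive oral administration of gabapentin capsule".
- **EA Combined With Medication Group:** "Patients in this group received EA combined with gabapentin".

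**The concern.** The section that defines the outcome is narrower than the two places that label it. On its literal terms, a painkiller bought without a prescription adds nothing to the outcome, although it is part of what the patient needed to control pain.

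The elimination criterion does not close this gap. It can act only on use that has come to light, and then it removes the patient instead of measuring the use. The Limitations section accepts that patients are difficult to blind, and no sham control is used. Whether a patient seeks extra pain relief may therefore depend on how well the allocated treatment works, or is believed to work.

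At stake is what the result means. A lower prescription dose in one arm could reflect less need for analgesia, a shift to uncounted products, or the loss of patients who took something else. The outcome as defined does not separate these.

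**Working it through.** The plan gives no figure for this outcome, so there is none to reproduce. The sample size (57 per group, raised to 66 per group and 132 in total) is based on the ZBPI and has no bearing here. The check is a comparison of texts and one identity.

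**1. What each text covers, read literally**

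| Pain relief taken | Secondary Outcome Measures | Abstract and Table 1 label | Fourth elimination criterion |
|---|---|---|---|
| Trial gabapentin | counted | counted | not triggered |
| Another prescribed analgesic | counted | counted | triggered if known and regarded as adjunctive |
| Non-prescription analgesic | not counted | counted | triggered if known and regarded as adjunctive |

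The last row is where the texts part. One text leaves the use out, another includes it, and a third removes the patient.

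**2. Does the outcome mean trial gabapentin alone?** Both arms are given gabapentin and no other analgesic, which favours that reading. The schedule fits it less well.

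- The outcome is a change from a week-0 value taken before the intervention, while trial gabapentin is started as part of the intervention.
- Table 2 excludes patients on antithrombotic drugs but none on analgesics, so a week-0 dosage can include whatever patients were already taking.
- The Intervention section ends the treatment course by week 6, yet the outcome is assessed again at week 14, when the analgesic in use need not be trial gabapentin.

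The wording therefore leaves the scope open.

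**3. What the prescription dose can show.** For argument only, suppose all analgesia could be put on one scale. Let T be total use, P prescription use and O other use, so that P = T − O. Write D for the mean in the EA arm minus the mean in the medication arm. Then

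D(P) = D(T) − D(O).

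- D(O) = 0: the prescription contrast equals the contrast in total need.
- D(O) > 0 (more other use with EA): the prescription contrast makes EA look more drug-sparing than it is.
- D(O) < 0 (more other use with medication alone): the prescription contrast hides part of any sparing.

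The documents give no value for O in either arm, so the sign of D(O) is unknown and so is its size.

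**4. What elimination does.** Removing every known user sets recorded O to zero among those who remain. The remaining groups have then been selected after randomisation, on behaviour that may follow from pain control. They are no longer the groups that were randomised, and the proportion removed may differ by arm.

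**The case against.** The strongest reply is that this is one adjective. The abstract and Table 1 use short labels and the outcome section gives the fuller name. With gabapentin the only analgesic provided in either arm, the prescription analgesic is most naturally the titrated trial drug. Other pain treatments are not an overlooked co-treatment, because the elimination criterion addresses them, and applying it presupposes that someone asks. A condensed article may leave the recording of concomitant drugs to the full protocol and the case report form, neither of which is shown.

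Much of this stands. The mismatch of labels alone is minor, and the gabapentin reading is plausible. It cannot be said that other analgesic use goes unrecorded, or that nothing in the trial's data could reveal it. What remains is that the article gives two scopes for one outcome, and that it handles other pain relief by removing the patient. A record of concomitant drugs elsewhere would change neither.

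A reader might also infer that an apparent drug-sparing effect would really be substitution. That needs more non-prescription use in the EA arm. The documents do not suggest this, and the opposite imbalance is at least as easy to imagine. Nor does the article's Conclusion announce a drug-sparing claim.

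**Conclusion.** The point holds as a minor one. The outcome's scope is stated in two ways. Under the narrower statement together with the elimination criterion, non-prescription pain relief is either outside the outcome or a ground for exclusion after randomisation that may be related to response. A difference in prescription dose, or its absence, should not be interpreted as a difference in total analgesic need.

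No magnitude can be given. Direction and size depend on how many patients in each arm use other analgesics and how much, and the documents are silent on both. The verdict rests on a literal reading of the definition and on taking elimination to mean that the patient leaves the comparison, since the article does not say otherwise.

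A reader might go further and infer that uncounted analgesics dilute the primary ZBPI contrast. The documents do not support a figure for that. Any such effect would come from the drugs being taken, not from how this secondary outcome is worded, and rewording the outcome would change no ZBPI score.

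**What to change.** 1. Reconcile the abstract, Table 1 and Secondary Outcome Measures into one definition that covers all analgesics taken, prescribed or not.
2. Record them at weeks 0, 2, 4, 6 and 14, the visits at which Table 1 already schedules this outcome.
3. Report two variables by arm: gabapentin in mg/day, and any other analgesic use (yes/no). The first keeps the titrated dose interpretable and the second shows whether use of other products differs.
4. State under Elimination Criteria that patients who use other analgesics stay in the randomised comparison, and that excluding them is only a sensitivity analysis.

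This concerns measurement and analysis and alters no dose or treatment rule. The cost is one more case report form item. The drawback is that recall of non-prescription use is imperfect, so the yes/no variable will miss some of it.
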